### Sample size calculation

The study will aim to recruit about 385 participants. This sample size gives 80 % power at the 5 % level of significance to detect an effect size of 0.32 standard deviations between conditions on the primary outcome measure, given a correlation of 0.5 between baseline and 24-week scores [56]. This effect size is the mean found in interventions designed to prevent anxiety in children and adolescents [57], and this sample size allows for an attrition rate of approximately 20 % at the final follow-up.

### Statistical analyses

Mixed-models analyses of variance will be conducted on all continuous outcomes to evaluate the effect of the intervention. The mixed-models approach is consistent with intention-to-treat analytic approaches under the assumption that data are missing at random. Any participants who are randomly assigned but withdraw from the study, or do not complete the intervention, will be included in these analyses as randomly assigned. Contrasts will compare change from baseline at the 12- and 24-week follow-ups between conditions as well as change between the 12- and 24-week follow-ups. Between-group effect sizes (Cohen’s *d*) will be calculated by standardising the differences between baseline and follow-up scores by the pooled standard deviation of the baseline scores. Responders will be identified as participants who demonstrate a statistically reliable improvement in anxiety symptoms on the PAS-R between baseline and T3, according to the procedures in Jacobson and Truax [52]. Response rates will be compared across conditions, and relative risk, the ratio of the probability of a response occurring in the intervention group versus the control group, will be calculated and tested for significance. The number needed to treat to achieve a response will be calculated with 95 % confidence intervals by using the method proposed by Bender [58].

Predictors of outcome will also be explored in addition to group allocation, including parent and child factors. The amount of program usage by intervention participants will be described, and predictors of program use will be explored. In addition to the intention-to-treat analyses, ‘per-protocol’ analyses will be conducted to examine the program’s effect in participants who have received an adequate ‘dose’ of the intervention. These exploratory analyses will evaluate the effectiveness of completing different amounts of the program (e.g., at least six modules). Statistical analyses will be conducted by using SPSS (IBM Corp, Armonk, NY, USA) and STATA (StataCorp, College station, TX, USA), and significance level will be set at a *P* value of less than 0.05.

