## Discussion

This study will provide important information about the efficacy of an online parenting program that aims to prevent anxiety problems in young children. It will build on previous efficacy [16] and translational [18] research into the Cool Little Kids parenting group program by broadening the program’s potential reach to an online audience. Internet-based delivery of the program could result in an easily accessible evidence-based resource to help families with young children at temperamental risk for anxiety disorders.

This study extends the small feasibility pilot of Cool Little Kids Online to a large RCT with a longer follow-up of participants. It builds on the pilot study by enhancing program aspects thought to improve adherence to online interventions. The RCT tests a different model of providing clinician support ‘on-demand’, which maximises the efficient use of study resources whilst acknowledging the positive effects on adherence and outcomes that clinician support can achieve [59]. Support on-demand balances the need for a low-cost solution that can be sustainable into the future with the expected benefits that support can provide to parents who especially need it. This RCT also innovatively tests the effects of a prize draw on reducing attrition at the final assessment point. This recognises that although conducting the study online can make it easier to recruit participants and reach the target sample size, greater ease in joining an online study can also increase the likelihood that some participants will drop out, resulting in higher rates of attrition than a non-online trial [60].

Prevention and early intervention approaches to anxiety disorders are important, as treatment alone cannot avert the entire population disease burden [61]. Parenting programs to prevent internalising problems in young children are relatively rare, even though corresponding parenting programs for externalising problems are established as effective [62]. To our knowledge, this is the first RCT of an online selective intervention aimed at preventing anxiety problems in young children.

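### The primary contrast of change from baseline makes inefficient use of baseline PAS-R: adjusting for it would raise power by about 8 points at the same sample size

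*Protocol article*

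**What the plan says.** Under Statistical analyses, the protocol article plans mixed-model analyses of variance for all continuous outcomes and includes everyone as randomised, assuming data missing at random. The treatment effect is defined by contrasts: "Contrasts will compare change from baseline at the 12- and 24-week follow-ups between conditions". Baseline is therefore one of the modelled time points. No baseline covariate is named, and nothing says that the two arms share a baseline mean.

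Under Sample size calculation: "The study will aim to recruit about 385 participants". The target is 80% power, at a 5% significance level, for a difference of 0.32 SD in PAS-R between the arms, "given a correlation of 0.5 between baseline and 24-week scores". Dropout is built in: "this sample size allows for an attrition rate of approximately 20 % at the final follow-up".

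The Enrolment and randomisation section places allocation, 1:1 by simple randomisation, at the end of the baseline questionnaire. Table 2 shows PAS-R at baseline, 12 weeks and 24 weeks.

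**The concern.** A between-arm difference in change subtracts the whole baseline score, whatever the correlation. Where that correlation is moderate, this adds about as much noise as it removes. At exactly 0.5 the two cancel, so the correlation quoted in the sample size paragraph buys no precision under the contrast as written. Below 0.5 the change contrast does worse than a comparison of follow-up scores alone.

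Because allocation follows the baseline questionnaire, the arms have the same expected baseline. An analysis that uses this fact is also valid and is more precise at every correlation below 1. At stake is power on the primary outcome, in a design sized to about 80% with little margin. The Discussion also acknowledges that easy online enrolment can lead to more dropout, "resulting in higher rates of attrition than a non-online trial".

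**Working it through.** **Inputs.** From Sample size calculation: effect d = 0.32 SD, power 80%, correlation r = 0.5 between baseline and 24 weeks, attrition 20%, 385 randomised. From Statistical analyses: "significance level will be set at a *P* value of less than 0.05". From Enrolment and randomisation: 1:1 allocation. Assumed, because the article does not state them: a two-sided test, equal SDs at baseline and 24 weeks, and equal dropout in the two arms.

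**Step 1. Reproduce 385.** The number per arm is 2(1.96 + 0.8416)² × vf / 0.32², where vf is the variance factor relative to a follow-up score alone.

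| Analysis | vf at r = 0.5 | Per arm | Completers | Randomised (÷ 0.8) |
|---|---|---|---|---|
| Follow-up score only | 1.00 | 153.3, so 154 | 308 | 385 |
| Change from baseline, 2(1 − r) | 1.00 | 153.3, so 154 | 308 | 385 |
| Baseline-adjusted, 1 − r² | 0.75 | 115.0, so 115 | 230 | 287.5, so 288 |

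The stated 385 is reproduced exactly with factor 1.0. It is not what an adjusted analysis would need. The ratio of adjusted to change-score variance is (1 − r²) / [2(1 − r)] = (1 + r)/2, which is 0.75 at r = 0.5 and below 1 for every r below 1.

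**Step 2. Power among completers.** With 154 per arm, d = 0.32, two-sided 0.05 and the noncentral t distribution:

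| r | Change contrast | Baseline-adjusted |
|---|---|---|
| 0.3 | 66% | 84% |
| 0.4 | 72% | 86% |
| 0.5 | 80% | 90% |
| 0.6 | 88% | 94% |
| 0.7 | 95% | 98% |

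A comparison of follow-up scores alone has 80% power whatever r is.

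**Step 3. Power under the planned mixed model.** This model also uses participants who have no 24-week score. Let n = 385/2 = 192.5 be randomised per arm and m be the number per arm with a 24-week score. In the simplest case, where dropouts supply baseline only:

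- Baseline means free: variance = 2[(1 − r²)/m + (1 − r)²/n].
- Common baseline mean: variance = 2(1 − r²)/m.

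At 20% attrition, m = 154:

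- Free: 2(0.75/154 + 0.25/192.5) = 0.01234, SE 0.1111. Then 0.32/0.1111 − 1.96 = 0.92, power 82%.
- Common: 2 × 0.75/154 = 0.00974, SE 0.0987. Then 0.32/0.0987 − 1.96 = 1.28, power 90%.

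If some or all dropouts also supply a 12-week score, both powers rise a little. A generalised least squares calculation over three visits, with the other inter-visit correlations assumed to lie between 0.5 and 0.7, gives 82–84% with free baseline means and 90–92% with a common mean. The gain is about 8 points throughout.

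**Step 4. Illustration at 40% attrition.** The documents give no such figure. With m = 115.5, the same calculation gives 73–78% with free means and 80–86% with a common mean, again a gain of about 8 points.

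**The case against.** The strongest objection is that the text does not fix the parametrisation. The article never says that baseline means are free, and in a constrained longitudinal model the 24-week effect is also a between-arm difference in change. The quoted sentence therefore does not exclude that model. Nor does the sample size settle the matter, since 385 also fits a follow-up-only comparison. This stands as a limit on certainty: free baseline means are the default reading of a mixed-model ANOVA with change contrasts, not a statement in the protocol. A fuller plan could specify adjustment, but the contrast as published does not.

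A second objection is that nothing is wrong: the contrast is unbiased under randomisation and has its promised power. That is correct. A reader might infer that 385 is miscalculated, that the trial is underpowered, or that the primary comparison is invalid. The documents support none of these.

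Third, completer-only figures overstate the gain, because the planned model keeps partial responders. This also stands: the 10-point gap at r = 0.5 becomes about 8. Saying that baseline contributes nothing is exact only with complete data. The gap also narrows above r = 0.5, and the documents give no reason to expect a lower correlation.

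Finally, a reader might take the Discussion as a forecast of attrition well above 20%. It says only that online enrolment can have this effect, as background to the prize-draw sub-study, and gives no rate.

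**Conclusion.** The point holds as an efficiency recommendation. On the default reading, and with complete data at the planned r = 0.5, the primary contrast is no more precise than an analysis that ignores baseline PAS-R; adjustment would cut its variance by a quarter. Under the planned mixed model at 20% attrition, the realistic gain is about 8 percentage points of power, from 82–84% to 90–92%.

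The conclusion rests on equal SDs over time, a two-sided test, equal dropout in the two arms, and assumed correlations of 0.5–0.7 for the visit pairs whose correlation the article does not give. The direction does not depend on r, but the size does: among completers the gain is 18 points at r = 0.3 and about 3 at r = 0.7.

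**What to change.** For PAS-R and every other continuous outcome measured at baseline, replace the unadjusted change contrast with one of these:

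- a constrained longitudinal mixed model: common baseline mean, time, group × post-baseline time, unstructured covariance; or
- a mixed model on the post-baseline scores, with baseline score and baseline × time as covariates.

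Name the adjusted between-arm difference at 24 weeks as the estimate. For the over-involved/protective parenting scale, which Table 2 shows at baseline and 24 weeks only, the same adjustment applies to the single follow-up.

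Keep 385 and state in Sample size calculation that power at r = 0.5 and 20% attrition is about 90% under this analysis.

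The cost is a change of analysis wording, with no new measurements or participants. It should be specified before outcome data are examined. At the submission date in Trial status (21 August 2015, after a June 2015 start), no 24-week score could yet have fallen due.

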## Discussion

This study will provide important information about the efficacy of an online parenting program that aims to prevent anxiety problems in young children. It will build on previous efficacy [16] and translational [18] research into the Cool Little Kids parenting group program by broadening the program’s potential reach to an online audience. Internet-based delivery of the program could result in an easily accessible evidence-based resource to help families with young children at temperamental risk for anxiety disorders.

This study extends the small feasibility pilot of Cool Little Kids Online to a large RCT with a longer follow-up of participants. It builds on the pilot study by enhancing program aspects thought to improve adherence to online interventions. The RCT tests a different model of providing clinician support ‘on-demand’, which maximises the efficient use of study resources whilst acknowledging the positive effects on adherence and outcomes that clinician support can achieve [59]. Support on-demand balances the need for a low-cost solution that can be sustainable into the future with the expected benefits that support can provide to parents who especially need it. This RCT also innovatively tests the effects of a prize draw on reducing attrition at the final assessment point. This recognises that although conducting the study online can make it easier to recruit participants and reach the target sample size, greater ease in joining an online study can also increase the likelihood that some participants will drop out, resulting in higher rates of attrition than a non-online trial [60].

Prevention and early intervention approaches to anxiety disorders are important, as treatment alone cannot avert the entire population disease burden [61]. Parenting programs to prevent internalising problems in young children are relatively rare, even though corresponding parenting programs for externalising problems are established as effective [62]. To our knowledge, this is the first RCT of an online selective intervention aimed at preventing anxiety problems in young children.

## Trial status

The study began in June 2015, and 270 participants had been recruited at the time of submission (21 Aug. 2015).

## Abbreviations

CALIS-PV: Children’s Anxiety Life Interference Scale – Preschool Version
DSM-IV: Diagnostic and Statistical Manual of Mental Disorders, 4th Edition
K10: Kessler 10 Psychological Distress Scale
OAPA: Online Assessment of Preschool Anxiety
OI/P: Over-Involved/Protective parenting scale
PAS-R: Revised Preschool Anxiety Scale
RCT: Randomised controlled trial
SDQ-ES: Strengths and Difficulties Questionnaire-Emotional Symptoms subscale
